#### Secondary outcomes

2.2.2

Mean BCVA according to the ETDRS charts.Mean macular sensitivity (MS).

#### Safety parameters

2.2.3

Cardiac and respiratory parameters (heart frequency, blood pressure, oxygen saturation, respiratory support).

### Data analysis plan and statistical analysis

2.3

The sample size was estimated based on epidemiological data and previous literature on AMD progression using planning assumptions for 12 months conversion to wet AMD. Eligibility criteria are reported in Table 1; in brief, contralateral wet AMD status (yes/no) will be recorded at baseline given its strong influence on conversion risk. Published evidence indicates that conversion risk depends substantially on fellow-eye status. In high-risk fellow eyes of patients with unilateral wet AMD, Barbazetto et al. (20) reported a 12-month conversion rate of 20.3% in MARINA and 15.9% in ANCHOR studies. In large trial populations with wet AMD in the contralateral eye, fellow-eye analyses reported cumulative incidences of approximately 26.2–32.2% over 96 weeks (21–23). In contrast, in cohorts without wet AMD in the contralateral eye, annual conversion rates are lower; for example, Chakravarthy et al. (24) reported progression to choroidal neovascularization (CNV) of approximately 3.2 per 100 person-years in bilateral early/intermediate AMD, compared with 15.2 per 100 person-years when CNV was present in the fellow eye (25). Therefore, the expected 12-month conversion rate of 12% has been used as a planning value reflecting the anticipated mix of baseline risk strata in our eye-level cohort, rather than a single incidence applicable to all included eyes. Observed conversion will be reported as stratified by the contralateral wet AMD status (yes/no), and the contralateral status will be included as a key prognostic factor in adjusted analyses.

Assuming a 12% progression rate in the solifenacin group and a 3% progression rate in the mirabegron group at 12 months (absolute difference 9%), with *α* = 0.05 (two-sided) and power = 80%, the required sample size is n ≈ 134 participants per group (net, without accounting for dropouts), computed using the standard formula for comparison of two proportions. The choice of the absolute difference of 9% is not based on clinical data as no clinical trials using either solifenacin or mirabegron to verify the rate of dry AMD progression to the wet form have been performed. This absolute difference was selected as a clinically meaningful planning effect size (Number Needed to Treat ≈ 11 over 12 months). Because eligibility and outcomes are defined at the eye level and participants may contribute with one or two eligible eyes, this calculation should be considered a planning approximation; all inferential analyses will account for within-participant correlation using robust standard errors clustered by participants.

To allow for an expected 15% dropout/non-compliance rate, the enrollment target was increased accordingly, yielding n ≈ 157 participants per group (314 total). For reporting and logistical reasons this has been pragmatically rounded to 156 participants per group (312 total); the protocol will state that this figure includes an allowance for approximately 15% attrition.

The sample size was computed according to the classical formula for two independent proportions:

$$n=\frac{\left(Z_{1-\frac{\alpha }{2}}\sqrt{2p(1-p)}+Z_{1-\beta }\sqrt{p_{1}(1-p_{1})+p_{2}{\left(1-p_{2}\right)}^{2}}\right)}{{\left(p_{1}-p_{2}\right)}^{2}}$$

Where *p*_1_ = 0.12, *p*_2_ = 0.03, *p* = (*p*_1_ + *p*_2_)/2, *α* = 0.05, and 1-*β* = 0.80. The resulting net sample size is approximately n ≈ 134 per group; after adjusting for ~15% attrition the enrollment target is *n* ≈ 157per group (rounded for the protocol to 156 per group).

All statistical analyses will be done using Python in the Google Colab cloud computing environment and/or SPSS (version 31). The primary confirmatory timepoint will be 12 months. To control type 1 error across the pre-specified primary endpoints, *p*-values will be adjusted using the Holm procedure (two-sided). Statistical significance will be set at a two-sided α = 0.05. Analyses will be conducted using exposure-defined (as-treated) and protocol-adherent approaches, rather than randomized intention-to-treat terminology. Continuous variables will be summarized as mean ± standard deviation or median with interquartile range, depending on the data distribution assessed by the Shapiro–Wilk test. Categorical variables will be presented as frequencies and percentages. Baseline characteristics will be described and group balance will be assessed using standardized differences, rather than relying on significance testing of baseline differences.

The primary outcome measures include conversion to wet AMD at 12 months, and outer retinal morphology parameters obtained from SD-OCT and FAF, including RPD type, ONL thickness, ChT, CMT, and FAF changes. These will be analyzed using mixed-effects models to account for repeated measures at T0, 6 months, and 12 months, with fixed effects including treatment group, time, and treatment×time interaction. Robust standard errors clustered by participants will be used to account for correlation between eyes from the same participant. Adjustments will be made for baseline BCVA, age, sex, AMD stage, contralateral wet AMD status (yes/no), and other relevant factors. If assumptions of normality are not met, appropriate non-parametric methods or robust modeling approaches will be used.

Secondary outcomes will consist of changes in BCVA (ETDRS letters) and mean MS (microperimetry). These will be analyzed using the same modeling method, with post-hoc pairwise comparisons adjusted for multiple testing using the Bonferroni method. Given the non-randomized design, primary analyses will use a pre-specified adjusted model including key baseline prognostic factors (age, sex, baseline BCVA, AMD stage/severity, comorbidities, baseline symptom severity, and contralateral wet AMD status), and results will be reported as effect estimates with 95% confidence intervals. Safety parameters (heart rate, blood pressure, oxygen saturation, need for respiratory support) will be reported as the number and percentage of patients with pathological values, without correlation to other variables. Adverse event rates will be compared using χ^2^ or Fisher’s exact tests.

Extreme values will be checked for plausibility and kept unless classified as data entry mistakes or physiologically unlikely. Missing data will be managed according to their missingness pattern, and sensitivity analyses will be conducted to assess the reliability of the results. Exploratory subgroup analyses will be performed according to AMD stage (early vs. moderate). Sensitivity analyses will exclude participants who stop taking mirabegron before 6 months or require a dose adjustment. In Figure 1, trial flow is schematically represented.

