#### Primary outcomes

2.2.1

Primary outcomes include conversion to wet AMD at 12 months (assessed by the presence of intraretinal fluid, subretinal fluid, pigment epithelial detachment, subretinal hyperreflactiva material) and outer retinal morphology using SD-OCT and FAF, including reticular pseudodrusen (RPD) type, outer nuclear layer (ONL) thickness, choroidal thickness (ChT), central macular thickness (CMT) and FAF changes.

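### The 80% power is for conversion alone at unadjusted two-sided α = 0.05, but conversion is tested in a Holm family with the other primary outcomes and has no priority there

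*Protocol article*

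**What the plan says.** **Sample size (Protocol article, section 2.3).** The calculation concerns conversion only: "Assuming a 12% progression rate in the solifenacin group and a 3% progression rate in the mirabegron group at 12 months". It uses the full significance level ("0.05 (two-sided) and power = 80" percent) and concludes that "the required sample size is n ≈ 134 participants per group (net, without accounting for dropouts"). A 15% allowance for dropout and non-compliance brings the target to about 157, and "this has been pragmatically rounded to 156 participants per group (312 total"). Multiplicity is not mentioned in this calculation.

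**Primary outcomes (section 2.2.1, repeated in 2.3).** Conversion at 12 months is listed together with outer retinal morphology, "including reticular pseudodrusen (RPD) type, outer nuclear layer (ONL) thickness, choroidal thickness (ChT), central macular thickness (CMT) and FAF changes".

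**Multiplicity (section 2.3).** "To control type 1 error across the pre-specified primary endpoints", p-values are Holm-adjusted, two-sided, against 0.05. Nothing puts conversion first, reserves α for it, or sets a testing order.

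**The concern.** Power belongs to a particular test at a particular significance level. Here it was worked out for one test at 0.05, while the plan tests that outcome as one of several under Holm. Holm compares the smallest p-value with 0.05 divided by the number of tests and relaxes the threshold only after each rejection. Unless other outcomes are rejected ahead of it, conversion therefore faces a threshold well below 0.05.

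At stake is how a null result on conversion would be read. The closing paragraph of the Discussion makes reduced conversion the question that the study is to answer. A reader would take the chance of missing the assumed effect to be 20%. Under the planned procedure it could be as high as about 44%.

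**Working it through.** **Inputs (section 2.3).** p1 = 0.12, p2 = 0.03, difference d = 0.09, mean p = 0.075, two-sided α = 0.05, power 80%, 134 per group net, 156 per group enrolled, 15% attrition. The listed primary outcomes number six: conversion, RPD type, ONL thickness, ChT, CMT and FAF changes.

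**Step 1: reproduce the stated figure.** The standard pooled formula is

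n = [z(1−α/2)·√(2p(1−p)) + z(1−β)·√(p1(1−p1) + p2(1−p2))]² / d²

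- √(2 × 0.075 × 0.925) = 0.3725
- √(0.1056 + 0.0291) = 0.3670
- n = (1.960 × 0.3725 + 0.8416 × 0.3670)² / 0.0081 = 133.3, rounded up to 134

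This matches the protocol. The square is misplaced in the formula as printed, but the intended standard formula gives the stated number.

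**Step 2: power at the Holm thresholds.** Rearranged, power = Φ[(√n·d − z(1−α/2) × 0.3725) / 0.3670]. At n = 134, √n·d = 1.0418.

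- α = 0.05: z = 1.960, power = Φ(0.849) = 80.2%
- α = 0.05/2 = 0.025: z = 2.241, power = Φ(0.564) = 71.4%
- α = 0.05/6 = 0.0083: z = 2.638, power = Φ(0.161) = 56.4%

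| Threshold | Power at 134 per group |
|---|---|
| 0.05/6 | 56.4% |
| 0.05/5 | 58.9% |
| 0.05/4 | 61.9% |
| 0.05/3 | 65.9% |
| 0.05/2 | 71.4% |
| 0.05 | 80.2% |

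With six tests, the first row applies when no other outcome is rejected ahead of conversion. The last applies only when all five others are rejected. Actual power is a mixture of these rows. It cannot be pinned down, because the protocol gives no effect sizes for the morphology outcomes.

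**Step 3: sensitivity.**
- *Evaluable number after attrition:* 156 × 0.85 = 132.6 per group gives 79.8% at 0.05, 70.9% at 0.05/2 and 55.8% at 0.05/6.
- *No attrition at all:* 156 per group gives 65.0% at 0.05/6.
- *Seven tests:* 54.3% at 134 per group.
- *Method:* exact enumeration of the chi-square test at 134 per group gives 57.9% at 0.05/6, so the shortfall does not come from the normal approximation.

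**Step 4: what 80% would need at the first step.** The formula gives 206 per group net at 0.05/6 (206/0.85 = 242.4, so 243 enrolled per group) and 162 at 0.05/2 (162/0.85 = 190.6, so 191 enrolled). The plan has 156.

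**The case against.** **The number of tests is not stated.** Section 2.2.1 can be read as two primary endpoints, conversion and morphology, with the parameters as components of the second. The first-step power is then 71.4%, not 56.4%. Six is the more natural reading, because section 2.3 refers to morphology parameters in the plural and defines no composite. The ambiguity is real all the same, and both figures should be given. On either reading the 80% is unsupported.

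**The calculation ignores eyes and covariates.** The unit of analysis is the eye, and the models are adjusted with clustered errors. The protocol calls its own calculation a planning approximation for the eye-level reason. This stands as a limit on the absolute figures. As an illustration on assumed inputs that the protocol does not give (25% to 75% of participants contributing two eyes, inter-eye correlation 0.1 to 0.5), the effective number per group runs from about 140 to 216. Power at 0.05/6 is then about 59% to 82%, against about 82% to 95% at 0.05. The levels move but the gap remains. The protocol's caveat concerns eyes within participants, not multiplicity. Covariate adjustment and confounding could move power either way.

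**A reader might infer that true or guaranteed power is 56%.** The document does not support that. The figure is a first-step floor under six tests and one observation per participant, and rejections among the other outcomes raise it.

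**A reader might call these co-primary endpoints.** That term usually means that all must succeed, in which case no Holm adjustment is needed. Holm implies multiple primary endpoints, with a claim possible on any one.

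**A reader might add that RPD type and FAF changes have no stated direction of benefit, or that CMT overlaps with the fluid signs defining conversion.** These are separate questions of endpoint choice. The first is detail that a condensed article commonly leaves to the full protocol or analysis plan. The second is not stated in the document, and Holm is valid under any dependence. Neither bears on the power.

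**Conclusion.** The mismatch is certain: the sample size rests on conversion at an unadjusted 0.05, and the analysis tests conversion under Holm with no priority. On the protocol's own approximation, power for conversion lies between about 56% and 80% with six primary tests, or between about 71% and 80% with two. The stated 80% is the upper end and is reached only if every other primary outcome is also rejected.

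These figures assume 12% versus 3%, 134 evaluable per group (55.8% in place of 56.4% at 132.6) and one observation per participant. The protocol says openly that the 9-point difference does not come from clinical data. The defect is an overstated power claim. Holm still controls the type I error, and nothing here suggests biased estimates or inflated false positives.

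**What to change.** **Minimum change.** State how many tests enter the Holm family, and restate power for conversion as a range: about 56% to 80% with six primary endpoints, or about 71% to 80% if morphology is one endpoint whose single test is then defined. This changes text only.

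**Alternative, to be settled before outcome data are seen.** Make conversion at 12 months the single primary endpoint, or the first in a fixed sequence, tested at two-sided 0.05. Test RPD type, ONL thickness, ChT, CMT and FAF changes with Holm only after conversion is significant. This restores the stated 80% under the planning assumptions with no extra patients.

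The cost of the alternative is that the morphology outcomes lose equal primary status. It is also more than a rewording: the study is registered and has ethics acceptance at two centers, so a protocol amendment and a registry update would probably be needed.

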Wet AMD is preceded by dry AMD, which is characterized by a gradual degeneration of macular cells and the presence of lipid deposits beneath the retina both contributing to central vision loss. According to the global percentage of dry AMD progression to wet AMD, around 10–15% of patients with dry AMD progress to the wet form (4). Although there is no cure for dry AMD, the pipeline of new treatments to slow its progression is expanding. Once wet AMD is established, anti-VEGF therapy is intended to manage rather than cure wet AMD with most patients experiencing sight loss over time despite regular treatment. Preventing conversion, therefore, has better prognostic value for sight. A number of modifiable risk factors have been found to be effective in slowing AMD progression, such as smoking cessation, and dietary and nutraceutical supplements. In this respect, nutraceutical treatments might limit eye disease progression (5, 6). Among them resveratrol has emerged as a promising agent for mitigating retinal damage (7, 8). Some therapeutic agents have also been licensed for eyes with dry AMD including complement factor inhibitors, which, on the other hand, are only available for individuals with late-stage dry AMD (9). There exists a need for drugs for earlier stages of dry AMD that effectively reduce the risk of progression. Targeting oxidative stress and chronic inflammation might represent an effective treatment as their complex interplay plays a key role in retinal diseases (10).

Potential concomitance between AMD and OAB gave rise to the possibility of investigating whether a therapy that efficiently counteracts OAB may also act on dry AMD progression to wet AMD. As for wet AMD, the global prevalence of OAB is expected to increase by 10.6% from 2020 to 2030 with an increasing trend depending on obesity, gender and age (8). While anticholinergics have been the cornerstone of OAB treatment for decades, their use has consistently been challenged by issues related to side effects and lack of bladder selectivity (11). In particular, there is indication that eye diseases including glaucoma (12) and dry eye disease (13) might occur as side effects of anticholinergic drug administration in OAB patients.

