### Study design and participants: inclusion, exclusion and drop out criteria

2.1

We planned an observational double arm non-randomized study in two centers to compare the safety and efficacy of either mirabegron (50 mg/day) or solifenacin (5 mg/day) in OAB patients. The protocol provides that ophthalmologists will be blinded regarding which patients have been treated with both drugs. We planned to enroll 312 subjects aged between 50 and 80 years with a diagnosis of early or moderate dry AMD, according to ARDS classification, and OAB. The patients will be enrolled at the Department of Ophthalmology of the University of Lublin, Poland and the University of Naples Federico II, Italy from December 2025 to October 2026. All patients will be followed for a 12-month period. The study will be conducted in compliance with the tenets of the Declaration of Helsinki, accepted by the local Ethics Committee, protocol numbers 2025a45673 at the University of Naples Federico II, Italy and KE-0379/97/2025 at the University of Lublin, Poland.

All study participants will provide written informed consent prior to enrollment and for the use of their clinical data for scientific research in an anonymized manner. Inclusion and exclusion criteria are summarized in Table 1.

**Table 1 tab1:** Inclusion and exclusion criteria.

Inclusion criteria
Age 50–80-year-old
Patients with early or moderate dry AMD in one or both eyes
Patients with wet AMD in the other eye
OAB treated for at least 6 months with either mirabegron or solifenacin
BCVA > 65 EDTRS letters
Exclusion criteria
Any contraindication to β-agonists or anticholinergics
Allergy to β-agonists or anticholinergics
Uncontrolled hypertension; tachycardia; atrial fibrillation; long QT or concomitant treatment with drugs that cause lengthening of the QT interval
Patients exposed to experimental drugs other than mirabegron or solifenacin, complement factor inhibitors, photobiomodulation therapy, transscleral lutein iontophoresis therapy or recent surgery (e.g., 3 months)
Recurrent urinary infections
Renal or hepatic failure
Signs of ocular inflammation
Any other ophthalmic diseases such as dry eye, glaucoma, acute or chronic uveitis, advanced cataract
Pregnancy

AMD, age-related macular degeneration; OAB, overactive bladder; BCVA, best corrected visual acuity; EDTRS, early treatment diabetic retinopathy study; QT interval, the time from the start of the Q wave to the end of the T wave in an electrocardiogram.

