The unit of analysis will be the eye. When both eyes meet eligibility criteria, both eyes will be included. The study will stop if severe hypertension, tachycardia, or atrial fibrillation develops; in this case, the opportunity to reduce the dose of mirabegron may be considered. The patient will have the right to withdraw their consent at any point during the study. Mirabegron displays no significant increase in major adverse cardiovascular events with a cardiovascular profile almost comparable to that of antimuscarinic agents. In our study, the safe profile of a 50 mg dosage will be associated with an increase of approximately 1 bpm for heart rate and 0.4–0.6 mmHg for systolic/diastolic blood pressure.

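### The stated analyses group or drop patients by treatment that may be taken after T0; none is stated to keep everyone under their T0 drug, and past use of the other drug is neither barred nor adjusted for

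*Protocol article*

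**What the plan says.** The study compares two treatments that patients already take. Section 2.1: "We planned an observational double arm non-randomized study in two centers". The exposure needed for entry is in Table 1: "OAB treated for at least 6 months with either mirabegron or solifenacin". No listed criterion concerns earlier use of the other study drug.

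Section 2.3 names the analysis approaches: "Analyses will be conducted using exposure-defined (as-treated) and protocol-adherent approaches, rather than randomized intention-to-treat terminology". It models treatment group, time and their interaction over T0, 6 and 12 months. It does not say how a patient who changes drug between those visits is classed.

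Section 2.3 also gives one analysis for discontinuation: "Sensitivity analyses will exclude participants who stop taking mirabegron before 6 months or require a dose adjustment". No counterpart is given for solifenacin.

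The pre-specified adjusted model covers age, sex, baseline acuity, AMD stage, comorbidities, symptom severity and fellow-eye wet AMD. Past use of the other study drug is not named.

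On events that may interrupt treatment, section 2.1 says: "The study will stop if severe hypertension, tachycardia, or atrial fibrillation develops". The same sentence mentions a possible reduction of the mirabegron dose.

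**The concern.** Without randomization, the cleanest fixed point is the drug in use at T0. Grouping by that drug means that nothing happening afterwards decides who is compared with whom. An as-treated analysis can move a patient to the other group, and a protocol-adherent analysis can remove the patient. Either is harmless only if those who change treatment have, given the covariates, the same conversion risk as those who do not.

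The protocol gives a reason to doubt that. The events named in section 2.1 (severe hypertension, tachycardia, atrial fibrillation) are cardiovascular, and the Discussion rests the study hypothesis on choroidal hypoperfusion. On that reasoning, patients who leave mirabegron for such events may differ in retinal risk. Taking them out of the mirabegron group would lower its rate whether or not the drug works.

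The mirabegron-only sensitivity analysis cannot detect this, because it removes the same patients from one group only.

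Past use of the other drug is a separate, smaller gap. The Introduction says of OAB therapy: "While anticholinergics have been the cornerstone of OAB treatment for decades". Some mirabegron patients may therefore have taken an anticholinergic first. If treatment history is related to OAB duration or general health, it is a possible confounder that the model leaves out.

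**Working it through.** **1. The plan's own figure.** Inputs from section 2.3: p1 = 0.12 (solifenacin), p2 = 0.03 (mirabegron), two-sided α = 0.05, power 80%. With the standard pooled formula and mean proportion 0.075:

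n = [1.96·√(2·0.075·0.925) + 0.842·√(0.12·0.88 + 0.03·0.97)]² / 0.09² ≈ 134 per group.

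This matches the plan. Enrolling 156 per group with 15% attrition leaves 156 × 0.85 = 132.6 evaluable, with power 79.8%. The sample size arithmetic is not in question.

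**2. As-treated classification with no drug effect.** Let the true 12-month rate be 12% in both T0 groups, which are of equal size. A share s of mirabegron users moves to solifenacin. Their risk is R times that of mirabegron users who stay, and they are counted under solifenacin. Then:

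- rate in those who stay on mirabegron: x = 0.12 / (1 − s + s·R)
- as-treated solifenacin rate: (0.12 + s·R·x) / (1 + s)

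For s = 0.10 and R = 2: x = 0.12/1.10 = 0.109. Solifenacin = (0.12 + 0.10 × 0.218)/1.10 = 0.129.

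| s | R | Mirabegron | Solifenacin | False difference | Approx. type I error |
|---|---|---|---|---|---|
| 5% | 2 | 11.4% | 12.5% | 1.1 points | 6% |
| 10% | 2 | 10.9% | 12.9% | 2.0 points | 8% |
| 10% | 3 | 10.0% | 13.6% | 3.6 points | 15% |
| 15% | 2 | 10.4% | 13.2% | 2.7 points | 10–11% |
| 10% | 1 | 12.0% | 12.0% | 0 | 5% |
| 10% | 0.5 | 12.6% | 11.5% | −1.1 points | 6% |

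The type I error uses 132.6 × (1 − s) and 132.6 × (1 + s) patients and an unadjusted normal comparison at two-sided 0.05. The last two rows show that there is no bias when leaving is unrelated to risk, and that it reverses when leavers are at lower risk. All values of s and R are assumptions.

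**3. Exclusion from one group only.** If the same 10% with R = 2 are dropped rather than moved, the mirabegron rate is again 10.9% and solifenacin stays at 12.0%, a false difference of 1.1 points. With R = 3 it is 12.0 − 10.0 = 2.0 points. If the rule covered both groups, and stopping were equally frequent and equally selective in each, the two shifts would cancel.

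**4. Past use.** No calculation is offered. The documents give neither the share of patients with past use nor its effect on conversion. The finding rests on setting Table 1 beside the covariate list: the first does not bar past use and the second does not name it.

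**The case against.** **Intention-to-treat does not apply without randomization.** Correct, and avoiding the term is no fault. A study without randomization can still group by drug at T0.

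**The article does not say that switchers are recoded to the drug they end on.** True. The model has treatment group as a fixed effect and mentions no time-varying exposure. A sensitivity analysis that excludes early mirabegron stoppers also implies that some main analysis keeps them. So it cannot be claimed that the plan will move switchers. What stands is that both named approaches permit classing or dropping by later treatment, and no analysis by T0 drug is stated.

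**The link between leaving mirabegron and risk is conjecture.** Largely so. Section 2.1 mentions stopping and a dose change, not transfer to solifenacin, and describes mirabegron's cardiovascular profile as close to that of antimuscarinics. Table 1 already excludes several cardiovascular conditions at entry. This limits the likely size of the bias but not the mechanism.

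**Medication history and switching rules are routine content of a fuller plan.** In part. The point here is directed at the choices the article does state: the analysis approaches, the one-sided exclusion and the covariate list. That list is in one place left open to further relevant factors.

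Three stronger readings are tempting, and the documents do not support them:

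- *That patients on both drugs at once are admitted.* The blinding sentence, "ophthalmologists will be blinded regarding which patients have been treated with both drugs", might suggest this, and one exclusion spares the study drugs: "Patients exposed to experimental drugs other than mirabegron or solifenacin". But the entry criterion offers one drug or the other in a two-arm study, and that exclusion has to spare drugs that entry requires.
- *That past solifenacin use pulls the mirabegron rate towards 12%.* Section 2.3 derives 12% from general AMD cohorts, not from a solifenacin effect. Giving that rate to current mirabegron users assumes the drug does nothing for them.
- *That moving a single event changes the result.* At the planned rates, about 4 against 16 events are expected among 133 per group (Fisher p = 0.009). At 5 against 15, p = 0.034, still below an unadjusted 0.05. Only at 6 against 14 does it reach 0.10.

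**Conclusion.** The concern holds as a design weakness that should be corrected. The stated approaches allow post-T0 treatment to decide group membership or inclusion, no stated analysis protects against that, and the only discontinuation analysis is one-sided. Under no true effect, 10% switching with twofold risk gives a false 2.0-point benefit, against a planned difference of 9 points. That figure rests on assumed switching and risk values, and on switchers being counted under solifenacin. It shows what is possible, not what is likely. The direction also depends on who leaves. Past use of the other study drug is a real but smaller gap, and its effect cannot be sized from the documents.

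**What to change.** 1. Make the main analysis a comparison by the study drug in use at T0, with every participant kept in that group through 12 months whatever treatment follows. Keep the 6- and 12-month eye examinations for those who change or stop. Report the as-treated and protocol-adherent analyses as sensitivity analyses, with a written rule for classing switchers.
2. Apply the discontinuation and dose-change sensitivity analysis to both drug groups by the same rule.
3. Record past use of the other study drug at T0, add it (yes/no) to the adjusted model, and add a sensitivity analysis in patients never exposed to it.

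**Cost.** Protocol wording and one medication-history item, best collected at enrolment because it is harder to recover later. No treatment rule changes. Item 1 dilutes a true effect. As a ceiling under the planning rates, if 10% left mirabegron right at T0 and then had the 12% rate all year, the group rate would be 0.9 × 3% + 0.1 × 12% = 3.9%. The difference would be 8.1 points and power about 69% instead of 80%. Later or rarer switching costs less. Part of the loss is recovered because the 15% allowance covers non-compliance as well as dropout, and non-compliant patients who are still examined would now count. The never-exposed subset will be smaller and should be read from its estimate and confidence interval.

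### For ONL, choroidal and central macular thickness, baseline covariates listed without a visit interaction would leave the treatment×time contrast unadjusted

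*Protocol article*

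**What the plan says.** All of this is in the protocol article, section 2.3, unless another section is named.

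- **Response.** The primary outcomes, which include ONL thickness, ChT and CMT, are to be analysed with "mixed-effects models to account for repeated measures at T0, 6 months, and 12 months". T0 is therefore one of the response rows.
- **Fixed effects.** The model is described "with fixed effects including treatment group, time, and treatment×time interaction". No other interaction is named.
- **Covariates.** "Adjustments will be made for baseline BCVA, age, sex, AMD stage, contralateral wet AMD status (yes/no), and other relevant factors". How they enter the model is not stated.
- **Purpose of the adjustment.** "Given the non-randomized design, primary analyses will use a pre-specified adjusted model including key baseline prognostic factors".
- **Time of the test.** "The primary confirmatory timepoint will be 12 months". Whether the test is of the difference in change or of the group difference at 12 months is not stated.
- **Secondary outcomes.** BCVA and macular sensitivity are described in section 2.3 as changes and in section 2.2.2 as means. Of their analysis the plan says: "These will be analyzed using the same modeling method".

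**The concern.** In a non-randomized comparison, the covariates are there to remove differences between the solifenacin and mirabegron groups that would produce different outcomes without any drug effect. When the outcome is followed from T0, the differences that matter for treatment×time are those that affect how fast an eye changes, not only where it starts.

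The protocol itself expects such a factor. Section 2.3 cites about 3.2 conversions per 100 person-years in bilateral early or intermediate AMD, against 15.2 when the fellow eye already has neovascularization. Section 2.2.1 defines conversion by signs such as fluid and pigment epithelial detachment. It is a reasonable inference, though the protocol does not say so, that fellow-eye status also affects change in thickness.

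If contralateral status is unequal between the groups and enters only as a main effect, the treatment×time estimate would be labelled as adjusted while still carrying that imbalance in full. ONL, ChT and CMT are primary outcomes under Holm control, so this would reach confirmatory tests.

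**Working it through.** The plan gives no figure on this point, so there is none to reproduce. Its sample-size figures concern binary conversion.

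**Step 1: algebra.** Let g be treatment (mirabegron = 1), c the baseline covariates and t the visit. With covariates as main effects:

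y(t) = a + τg + δ(t) + θ(t)g + γc + error

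Subtracting T0 from 12 months, with δ and θ set to zero at T0:

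y(12) − y(0) = δ(12) + θ(12)g + error difference

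The term γc is gone. With complete data, the estimate of θ(12) is mean change on mirabegron minus mean change on solifenacin, with or without c.

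With covariate×visit terms κ(t)c, the change becomes δ(12) + θ(12)g + κ(12)c, and θ(12) is adjusted for c.

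**Step 2: size of what is left.** The bias in the crude contrast is

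(difference in mean c between groups) × (effect of c on 12-month change).

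The documents give neither factor. If wet-fellow eyes lose an assumed 4 units more by month 12, then:

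| Imbalance between groups (assumed) | Bias |
|---|---|
| 0 points | 0 |
| 10 points | 0.10 × 4 = 0.4 |
| 20 points | 0.20 × 4 = 0.8 |
| 30 points | 0.30 × 4 = 1.2 |

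**Step 3: simulation with two-eye clustering.** From the plan: 156 participants per group, three visits, standard errors clustered by participant. Assumed:

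- No drug effect.
- Contralateral wet AMD in 30% of mirabegron and 60% of solifenacin participants; these contribute one eye, the others two.
- Mean age 4 years lower on mirabegron.
- A wet fellow eye lowers the level by 8 and the 12-month change by 6; each year of age lowers them by 0.3 and 0.15.
- Standard deviations of 10 (participant), 8 (eye) and 4 (residual), treated as known. Units are arbitrary.
- 150 simulated trials per scenario.

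Expected crude bias:

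- Wet-fellow share of mirabegron eyes: 0.3/(0.3 + 0.7×2) = 0.176.
- Wet-fellow share of solifenacin eyes: 0.6/(0.6 + 0.4×2) = 0.429.
- Bias: (0.176 − 0.429)(−6) + (−4)(−0.15) = 1.51 + 0.60 = 2.11.

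Results, complete data:

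| Model | Treatment×12-month (SE) | Rejected at 5% | 12-month group difference |
|---|---|---|---|
| No covariates | 2.148 (0.600) | 95% | 5.867 |
| Main effects | 2.148 (0.600) | 95% | 1.301 |
| Covariate×visit | 0.043 (0.563) | 8% | 0.246 |

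The first two models never differed by more than 8e-15 in the treatment×12-month term. The mean of 2.148 agrees with 2.11 within Monte Carlo error (0.600/√150 = 0.049).

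With loss at 12 months of 12%, or 24% where the fellow eye is wet (assumed):

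| Model | Treatment×12-month | Rejected at 5% | 12-month group difference |
|---|---|---|---|
| No covariates | 2.009 | 93% | 5.437 |
| Main effects | 2.013 | 93% | 0.962 |
| Covariate×visit | −0.029 | 7% | −0.137 |

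The largest difference between the first two models in any trial was 0.03. Monte Carlo error for a true 5% rate is √(0.05×0.95/150) = 1.8 points, so 7% and 8% are compatible with 5%.

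**The case against.** The best defence is that the article does not fix the model criticised here. Its list of fixed effects is open, the form of covariate entry is not given, and a fuller analysis plan may contain covariate×visit terms. The tested contrast is also not named, and a 12-month group difference does respond to main-effect covariates (5.867 to 1.301 in the simulation). Both points stand, so the finding is conditional on the plain reading. They do not dispose of it: the article goes as far as naming response times, fixed effects and covariates, the only interaction it names is treatment×time, and under the alternative contrast part of the bias remains.

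Several stronger readings are tempting, but the document does not support them:

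- **That adjustment is the only protection against confounding.** A within-eye change contrast already removes additive, time-constant differences in level, measured or not. What it leaves is confounding of change.
- **That the defect is equally certain for BCVA and macular sensitivity.** Section 2.3 calls these outcomes changes. If change is the response, T0 is not a response row, main effects do adjust, and baseline BCVA is not used twice. The problem arises only if T0 is kept as a response.
- **That the fallback abandons adjustment and clustering.** The sentence reads: "If assumptions of normality are not met, appropriate non-parametric methods or robust modeling approaches will be used". It allows robust modelling, and section 2.3 elsewhere requires participant-clustered standard errors in all inferential analyses.
- **That the T0 outcome must become a covariate.** Table 1 requires at least 6 months on either drug before entry, so T0 is an on-treatment value. Conditioning on it may remove part of an effect already present; that is a choice of estimand.

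**Conclusion.** The point holds for ONL, ChT and CMT, conditional on main-effect entry of the covariates, which is the plain reading but an inference. Under that reading the treatment×time contrast is the crude difference in change: exactly so in a linear model with complete data, and to within 0.03 on an estimate of about 2.0 in the dropout scenario. That defeats the purpose for which section 2.3 introduces the adjusted model.

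The cancellation does not depend on the simulation settings. The size of the bias does: it is zero if the groups are balanced on the factors that drive change, and the value of about 2.1 units belongs to one assumed imbalance. The documents give no basis for a forecast in microns or letters.

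The point does not reach 12-month conversion, the outcome on which the study is sized, because eligible eyes are unconverted at T0. It should be settled before the data are analysed.

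**What to change.** In section 2.3:

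1. Name the treatment contrast tested at 12 months for each continuous outcome: difference in change from T0, or adjusted group difference at 12 months.
2. Add a covariate×visit interaction for each listed confounder, at least contralateral wet AMD status, AMD stage, age and baseline BCVA. Keep the participant-clustered standard errors.
3. For BCVA and macular sensitivity, say whether the response is the visit value with T0 as a row, in which case item 2 applies, or the change itself.
4. If wanted, give an analysis adjusting for the T0 value of the same outcome as a sensitivity analysis, noting that T0 follows at least 6 months on either drug.

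The cost is wording and a few parameters. With three visits, each single-coefficient covariate adds two terms, so the four named add 4 × 2 = 8. No data collection changes. The terms deal only with measured confounders of change; unmeasured ones remain a limitation of the design.
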